#### 2.2.1. Collecting Packs from Tobacco Retailers

The data collection team will determine a central point (such as a bus station, a government building, or a market place) in each PSU. All types of shops, such as tea stalls, kiosks, supermarkets, department stores, and cigarette shops that sell cigarettes or birri, or both, would be eligible to take part in the study. Enumerators will walk half a kilometer in both directions on the main street around the public gathering place and approach all the retailers meeting the eligibility criteria. All eligible retailers will be provided with both verbal and written information about the study. If they agree to take part, they will be required to sign the consent form. Following consent, the field worker will proceed to pack collection. The retailers would be supplied with a “collection bag” on the previous day and asked to keep all the empty packs resulted from loose sale on the following day since the shop opened in that bag. All “collection bags” will be retrieved by the field workers at the end of the business day. We will provide a small monetary reward of BDT 3 (GBP 0.03) per empty pack deposited in the collection bag. In case the empty pack of the cheapest and popular brands were not available in the bag from a particular retailer, the team would take a picture and code all the relevant attributes of such pack observed in the shop itself [3]. 

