This protocol will present a mixed-methods study to estimate the extent of illicit cigarette trade in Bangladesh. Three research questions will be addressed: (a) What proportion of cigarettes sold as retail in Bangladesh are illicit? (b) What are the common types of tax avoidance and tax evasion in Bangladesh? (c) Can pack examination from trash recycle market be considered as a new method to assess illicit trade in comparison to that from retailers and streets? Findings from this study will help policy makers develop more effective tobacco control measures and refute industry claims in Bangladesh. 

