## 2. Materials and Methods 

Measuring illicit tobacco trade is a complex task due to the illegal nature of the activities involved [2]. Various methods have been used to assess the extent of illicit trade, such as measuring the difference between consumption and tax paid sales, interviewing smokers, studying features of cigarette packs and econometric modeling, each having their own strengths and weaknesses [3,4,12,13]. We will use observational methods and collect data from empty cigarette packs from three sources: (a) from the retailers resulting from their loose cigarette sale [3,14]; (b) littered packs from the streets surrounding the retailers [3,15,16]; and (c) littered packs from trash recycle market. The last one can be considered as an innovation in the methodology for not being applied before and could be particularly useful in LMICs where trash recycle markets are established. Regardless of the pack source, such observational studies provide a direct way to assess illicit trade [7,17].

Once collected, we will examine certain characteristics of cigarette packs such as “no mention of retail price”, “mention of brand element”, “no graphic and textual health warnings”, “no declaration”, “a duty-free sign”, and “absence of correct and authentic tax stamps” of cigarette packs as indicators of being illicit [12]. Such information could also be collected either directly from tobacco users and/or by inspecting tobacco users’ packs. However, as “loose selling” of cigarettes is common and permitted by law in Bangladesh, consumer surveys and pack inspections are of limited use. On the other hand, loose selling makes retailer pack collections more relevant. We will therefore adopt the approach developed by John and Ross (2018) [3] to measure the extent of illicit cigarette sold as retail in Bangladesh. In addition, a structured questionnaire will be used to collect information from retailers selling cigarettes.

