#### 2.2.4. Interview of Point of Sale Retailers

During bag collection, basic information such as name and type of the store, price and estimated quantity of the cheapest brand sold in the shop, name and price of most popular brand, and the estimated quantity sold will be collected. In addition, they will be asked about the profit share of tobacco products in their total daily profit, sources of supply, incentives from the suppliers’ end, market supervision, and knowledge, understanding, and perception regarding illicit tobacco products. A structured questionnaire that has been used in studies in the UK, Bangladesh, Nepal, and Pakistan previously will be adapted to collect these data from the retailers [19]. Following the Tobacco Advertisement and Promotion Survey (TAPS) [20], a standard pack analysis tool has been developed. 

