Another important potential limitation of the proposed methodology would be its ability of correct estimation for the size of illicit market. Since the unit of observation from where packs would be collected is retail cigarette shops, selection bias might remain present in the estimation. The estimate would be overestimated if pack collection takes place in an area where illegal tobacco products are known to be traded. In contrast, the estimates would be underestimated if retailers purposefully preserve the licit cigarette packs in the collection bag. Moreover, conditioning that illicit cigarettes are sold in full packs in general rather than single sticks, collecting empty packs from retailers might underestimate the magnitude. Considering all these potential threats, we expect the study would be free from selection bias as the retailer selection would be completely random covering the urban–rural and border–non-border perspective around the country. The validity and representativeness of the estimate measured using the packs collected from retailers would be ensured by comparing that with the estimate retrieved from littered packs from the streets and packs collected from the trash recycle market in the same neighborhood. Estimates from the two later sources to a greater extent would address the limitations if retailer deposit only licit packs or illegal cigarette happens to be sold in full pack. The comparison of results and further analysis of illicit packs from these three sources would help us to examine the existence of any systematic difference among them. Absence of systematic difference would ensure the possible unbiasedness of the estimates [12].

Finally, in the absence of any prevalence data at the division or district level, it would not be possible to propose a sample size weighted on the local smoking prevalence or smoking intensity. Bangladesh has completed two rounds of Global Adult Tobacco Survey (GATS). However, the first round does not have district level or divisional level information on smoking prevalence while the data from second round have not been released yet. 

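### The retailer arm estimates the illicit share of packs opened for loose sale, not of all cigarettes sold at retail as question (a) asks, and random selection of shops does not close that gap

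*Protocol article*

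**What the plan says.** Research question (a), in section 1, asks "What proportion of cigarettes sold as retail in Bangladesh are illicit". The retailer source is narrower. Section 2 defines it as empty packs "from the retailers resulting from their loose cigarette sale", and under section 2.2.1 retailers are "asked to keep all the empty packs resulted from loose sale on the following day", with the bag retrieved at close of business. There is one supplement: where the cheapest and popular brands are missing from a shop's bag, "the team would take a picture and code all the relevant attributes of such pack observed in the shop itself".

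Section 4 sees the difficulty: "conditioning that illicit cigarettes are sold in full packs in general rather than single sticks, collecting empty packs from retailers might underestimate the magnitude". The same paragraph nevertheless continues: "we expect the study would be free from selection bias as the retailer selection would be completely random". It then relies on the street and trash estimates, which to a large extent "would address the limitations if retailer deposit only licit packs or illegal cigarette happens to be sold in full pack".

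Other provisions that bear on the point:

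- Section 3 analyses the three sources separately, triangulates retailer with street, and compares both with trash.
- Section 3 sets the illegal duty-free share in littered packs to the retailer share whenever the littered share is higher, and treats trash packs similarly.
- Section 2.2.3 includes trash packs only where a recycle market exists and packs can be obtained, and says such markets are limited in rural areas.
- Section 2.2.4 gives examples of interview items, among them "price and estimated quantity of the cheapest brand sold in the shop" and the quantity of the most popular brand.

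**The concern.** A pack sold whole leaves the shop with the buyer. It is not in the bag, and it is seen in the retailer arm only if its brand happens to be one of those coded on the shelf. What is measured is therefore the illicit share among loose-sold packs. That equals the share asked for in question (a) only if illicit and licit packs are opened for loose sale equally often.

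Section 4 answers this with random selection of retailers. Even taken at face value, that argument concerns which shops are observed. The problem is which sales within a shop are observed, and no selection of shops alters that.

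The stake is the use of the result. The study is meant to give an independent estimate and to counter industry claims, and section 1 cites a claim of about 2%. Close to that level, an understated retailer figure could appear to support the claim.

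**Working it through.** The plan states no figure on this point, so there is none to reproduce. The check is an identity, followed by illustrations.

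**Notation.** P is the true illicit share of packs sold at retail, L the share of all packs that are opened for loose sale, and s the share of illicit packs that are sold whole.

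**What the bags estimate.** Illicit loose-sold packs make up P(1 − s) of all packs, and all loose-sold packs make up L. The bag share is therefore

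R = P(1 − s) / L.

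- R = P only if s = 1 − L.
- R < P if s > 1 − L, that is, if illicit packs are sold whole more often than packs in general.
- R > P if s < 1 − L.

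The numbers of shops and postcodes do not appear, so a larger or better randomised sample does not move R towards P. The shop-coded packs are left out of the identity. They enter by brand and not in proportion to sales, so they do not turn R into an estimate of P.

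**Inputs.** P is set to 2% (the claim following industry estimates) or 16.8% (the figure for low- and middle-income countries), both from section 1. L and s are assumed; section 2 says only that loose selling is common.

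| P | L | s | R = P(1 − s)/L |
|---|---|---|---|
| 2% | 0.7 | 0.30 (= 1 − L) | 0.02 × 0.70 / 0.7 = 2.00% |
| 2% | 0.7 | 0.50 | 0.02 × 0.50 / 0.7 = 1.43% |
| 2% | 0.7 | 0.75 | 0.02 × 0.25 / 0.7 = 0.71% |
| 2% | 0.7 | 0.90 | 0.02 × 0.10 / 0.7 = 0.29% |
| 2% | 0.9 | 0.90 | 0.02 × 0.10 / 0.9 = 0.22% |
| 16.8% | 0.7 | 0.50 | 0.168 × 0.50 / 0.7 = 12.0% |
| 16.8% | 0.7 | 0.75 | 0.168 × 0.25 / 0.7 = 6.0% |
| 16.8% | 0.7 | 0.90 | 0.168 × 0.10 / 0.7 = 2.4% |

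In these cases R/P runs from 1.00 down to 0.11 (0.22 / 2). The direction can also reverse: with P = 2%, L = 0.7 and s = 0.1, R = 0.02 × 0.9 / 0.7 = 2.57%.

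**Whether the other arms repair it.** The section 3 rule sets the illegal duty-free share in litter to DF_R if DF_L > DF_R, and to DF_L otherwise. DF_R comes from the loose-sale sample. Take an assumed DF_L = 3%:

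- If illegal duty-free packs are sold only whole, DF_R = 0 and the adjusted street share is 0%.
- If DF_R = 0.5%, the adjusted street share is 0.5%.

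For this component the loose-sale restriction passes into the arm that is meant to correct it, and the trash arm is adjusted in the same way. The formula is written for duty-free packs only. Other non-compliant packs sold whole can still show in the street sample.

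**The case against.** The limitation is disclosed, its direction is stated and a response is designed. Street packs come from the streets where the retailers trade, so packs bought whole and discarded there can be sampled. A retailer–street gap is the signal that would reveal under-capture in the bags. Loose-sale collection is a reasoned choice, justified in section 2 by local practice and an existing published approach, and section 4 says funding limits the collection of unopened packs. All of this stands, and it rules out several stronger readings that a reader might infer:

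- **That the study cannot see whole-pack sales.** The street arm can, in part. The restriction applies to the retailer arm and, through the cap, to the duty-free component of the other two.
- **That whole packs have no chance at all of being observed in shops.** Section 2.2.1 provides for some shelf-coded packs, although these are brand-specific.
- **That nothing collected measures whole-pack volume.** The list in section 2.2.4 is open, and the questionnaire is not shown.
- **That the retailer figure is known to be too low, by a computable amount.** Section 4 speaks conditionally and the document gives neither L nor s. Any range is an assumption, and assuming a higher illicit share among whole packs builds the understatement in.

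The objection does not rescue the random-selection argument, and it does not show how the cap could be harmless if duty-free packs are mainly sold whole. A retailer–street gap also does not size the whole-pack effect by itself. Section 4 notes that retailers may withhold illicit packs, and section 3 notes that litter may include packs bought legally duty-free or abroad.

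**Conclusion.** The point holds for the retailer arm: it estimates the illicit share of loose-sold packs, plus a few shelf-coded brands, while question (a) asks about all retail sales. The estimate is too low if illicit packs are sold whole more often than licit ones, unbiased in this respect if they are sold whole equally often, and too high in the reverse case. The tabulated values show what is possible under assumed L and s; they do not estimate the bias, which cannot be derived from the document. The claim of freedom from selection bias through random retailer selection does not follow. The street and trash arms are a partial remedy, because of the duty-free cap and the limited rural reach of trash markets. The change should be made, since it affects what the study may conclude under question (a).

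**What to change.** 1. Label the retailer result 'illicit share of loose-sold packs' wherever it is reported. This is a wording change, possible even after fieldwork.
2. Remove from section 4 the statement that random retailer selection frees the study from this bias. Keep the acknowledgement that whole-pack sale could lead to underestimation.
3. Unless the questionnaire already has it, add one item at the bag-collection visit: how many packs were sold whole, and how many were opened for loose sale, on the bag day.
4. Answer question (a) by reporting the retailer and street estimates side by side, the street estimate with and without the duty-free cap. The uncapped version may include legally bought duty-free packs, so both are needed.
5. Show any volume-weighted combination, L × R + (1 − L) × W with W the illicit share of whole-pack sales, only as a sensitivity range. W is not observed. Litter may mix empties from loose and whole-pack sale, so using the street share for W is itself an assumption.

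The cost is one questionnaire item at a visit already planned, plus wording and one extra line of results. The downside is that the whole-pack count is reported by the retailer and the answer to question (a) becomes a range.

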#### 2.2.2. Collecting Discarded Packs from Streets

In addition to collecting empty packs from the tobacco retailers, discarded packs from the streets where those retailers are established and also from some other locally important streets around public gathering places will be accumulated [3]. The distance that would be covered in each street would be one kilometer (half a kilometer in each direction). The field workers would use separate “collection bag” with unique identification number for collecting the discarded packs in each area. The pack collection from streets would take place simultaneously during the day when the “collection bag” to the retailers would be distributed. The street selection would also consider the street condition for walking and possibility of finding littered packs. Necessary safety equipment such as masks and gloves will be provided to the field staff while collecting littered packs. 

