In general, all pack characteristics considered for detecting legitimacy in the retailer sample might also be accepted for those in littered or trash samples. Nevertheless, one of the limitations of the above general approach is that it might fail to distinguish between tax evasion and avoidance. More specifically, there may be some legally purchased duty-free packs as well as those bought from neighboring countries, in a sample from street, while also having illegally purchased and illegally sold packs in the retail shops belonging to that street. This possibility might result in under- or overestimation of the illicit cigarette trade. Hence, it rationalizes the application of an adjustment factor while measuring the magnitude of illicit cigarette in the sample collected particularly from street and trash recycle market. Table 3 exemplifies a thematic presentation of legitimacy criterion of a cigarette pack and adjustment requirement in the estimation. 

Assuming that the littered packs in the streets would by and large reflect the average characteristics of those sold by different retailers on the same street, the following adjustment method would be applied:

Suppose DF_L_ is the proportion of duty-free packs (both legal and illegal) in the littered sample and DF_R_ is the proportion of duty-free packs (all illegal) in retailer sample. Then, the estimated proportion of illegal duty-free packs from littered sample would be
=DF_R_ if DF_L_ > DF_R_; and
=DF_L_ if DF_L_ ≤ DF_R_.   

Similar adjustment process would be followed while estimating extent of illicit cigarette using packs from trash recycle sample. It should be noted here that self-made cigarette using tax-paid tobacco powder or crushed tobacco may not be the scope of current work. However, a pack for a local category of cheap cigarette known as “birri” would be collected and examined for its compliance as per the study definition. Statistical Analysis (STATA) software version 15 would be used. The main statistical analysis will report the frequencies and proportions of cigarette packs that do not comply with the tobacco control laws and falls within the study definition of illicit. 

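### The street sample mixes litter from the retailers' street with litter from other hand-picked streets, but the duty-free adjustment is justified only for litter from the retailers' own street

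*Protocol article*

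**What the plan says.** Section 2.2.1 fixes where retailers come from: "Enumerators will walk half a kilometer in both directions on the main street around the public gathering place and approach all the retailers" that are eligible.

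Section 2.2.2 defines the street sample in two parts. The first is "discarded packs from the streets where those retailers are established"; the second follows in the same sentence: "and also from some other locally important streets around public gathering places will be accumulated". On the choice of streets it adds: "The street selection would also consider the street condition for walking and possibility of finding littered packs". Bags carry a unique number per area; the text does not say per street.

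Section 3 introduces the duty-free adjustment with the assumption that "littered packs in the streets would by and large reflect the average characteristics of those sold by different retailers on the same street". It then states that DF_L "is the proportion of duty-free packs (both legal and illegal) in the littered sample", and that DF_R is the corresponding proportion among retailer packs, all of them illegal. The estimated illegal duty-free proportion is DF_R when DF_L exceeds DF_R, and DF_L otherwise.

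Section 3 also triangulates the retailer and street estimates and uses both as the reference for the trash-market method. Section 4 relies on the comparison of sources within the same neighbourhood to support the validity of the retailer estimate.

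**The concern.** The two provisions do not fit together. The sampling text takes in litter from streets where the protocol enrols no retailer, while the adjustment is justified street by street. Nothing in the article restricts DF_L to the retailers' own streets.

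Two results depend on this. The first is the adjusted duty-free component of the street estimate. The second is the reading of any gap between the street and retailer estimates. Section 4 expects litter to reveal what retailer bags miss, namely withheld illicit packs and whole-pack sales, and treats the absence of systematic difference as support for unbiasedness. If part of the litter comes from different streets, a gap may reflect the streets and not retailer behaviour, and agreement may be fortuitous. The extra streets are also not a random sample of the post code, because walkability and expected yield of packs enter the choice.

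**Working it through.** **What the text settles.** The plan states no figure for this point, so there is nothing to reproduce.

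| Item | Retailer sample | Street sample |
|---|---|---|
| Where | Main street, half a kilometre each way (2.2.1) | Retailers' streets plus other streets (2.2.2) |
| How chosen | All eligible retailers approached | Streets chosen by judgement |
| Proportion used | DF_R, retailer sample (3) | DF_L, whole littered sample (3) |
| Premise | n/a | Litter resembles same-street retail (3) |

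The premise covers the first part of the street sample. For the second part there are no same-street retailer data.

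**The rule as a formula.** Let R = DF_R, S = duty-free proportion in litter from the retailers' streets, O = duty-free proportion in litter from other streets, and w = share of litter packs from other streets. Then

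- pooled DF_L = (1 − w)S + wO
- pooled result = min(R, (1 − w)S + wO)
- matched result = min(R, S)

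**Direction.**

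- If S ≥ R, the matched result is R, the most the rule can return. Pooling can only lower it or leave it unchanged.
- If S < R, the matched result is S. Pooling raises it when O > S, to at most R, and lowers it when O < S.
- If O = S, pooling changes nothing.

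**Illustrations.** R = 2% throughout. The documents give none of R, S, O or w, so all values are assumptions.

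| S | O | Matched | w = 25% | w = 50% | w = 75% |
|---|---|---|---|---|---|
| 2% | 0% | 2.0% | 1.5% | 1.0% | 0.5% |
| 2% | 1% | 2.0% | 1.75% | 1.5% | 1.25% |
| 2% | 3% or 6% | 2.0% | 2.0% | 2.0% | 2.0% |
| 3% | 0% | 2.0% | 2.0% | 1.5% | 0.75% |
| 3% | 1% | 2.0% | 2.0% | 2.0% | 1.5% |

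For example, with S = 2%, O = 0% and w = 50%: 0.5 × 2% + 0.5 × 0% = 1.0%, and min(2%, 1.0%) = 1.0%.

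For the other case, S < R, take S = 1%, O = 5% and w = 50%. Pooled DF_L = 0.5 × 1% + 0.5 × 5% = 3%, so the rule returns 2% against a matched 1%. With O = 0% it returns 0.5%.

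**Illicit packs of other kinds.** The written cap covers duty-free packs only, so a street proportion without that cap can move either way. If 5% of retailer-street litter is illicit and w = 50%:

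- other streets at 1%: 0.5 × 5% + 0.5 × 1% = 3.0%
- other streets at 10%: 0.5 × 5% + 0.5 × 10% = 7.5%

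**The case against.** The same-street condition is written only for the adjustment. Section 4 speaks of sources in one neighbourhood, and Section 2 describes the litter as coming from streets around the retailers. Streets near the central gathering place plausibly meet that description. A reader might infer that the triangulation is also stated to be same-street; the text does not say so. For triangulation, comparability is only implied.

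The assumption is also loose. It is qualified as holding by and large, concerns averages, and is applied to sample-level proportions. A reader might infer that it must fail on the extra streets. It need not: it holds if main-street retailers resemble those nearby. What is missing is support for it, not the possibility that it is true. The mismatch is also partial, because the retailers' own streets are in the litter sample.

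On size, the 1% to 2% example might suggest that pooling doubles the adjusted figure. That case needs S below R. DF_L counts legal and illegal packs and DF_R only illegal ones, so under the plan's own premise S should be at or above R apart from sampling variation. With S = 2% and the same O = 5%, pooled DF_L is 3.5% and the rule still returns 2%, so there is no error. Duty-free is also only one of seven illicit attributes.

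Finally, wider litter coverage serves a purpose. Packs are carried before being dropped, so even retailer-kilometre litter is not perfectly matched, and the trash market is not street-specific at all. The number of extra streets and the meaning of an area for bag numbering may be settled in the full protocol.

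These points limit the claim. They do not remove the misfit between two provisions that the article itself states.

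**Conclusion.** The point holds in limited form. The premise of the duty-free adjustment is unsupported for that part of DF_L which comes from streets without sampled retailers. The retailer-street comparison is partly confounded by differences between streets, although the plan describes that comparison only at neighbourhood level.

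The size cannot be computed, because neither the share of litter from other streets nor its illicit proportion is given. The effect is zero if the streets are alike. If matched DF_L is at or above DF_R, pooling can only lower the duty-free component; if it is below, the component can move either way. The documents do not support a claim that the adjusted figure is inflated, that it is wrong by any particular factor, or that the triangulation is invalid. As planned, the data may simply be unable to show whether the extra streets matter.

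**What to change.** - At collection, put litter from the retailer kilometre and litter from other streets in separate bags, and record street type in the bag number. Section 2.2.2 already requires unique numbers per area, so this is one more field.
- Compute DF_L, the adjustment and the main retailer-street comparison on retailer-kilometre litter.
- Report other-street litter as a separate estimate, and the all-litter estimate as a sensitivity analysis. This keeps the wider coverage and shows whether the streets differ.

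The cost is fewer packs, and so less precision, in the matched comparison. No extra fieldwork is needed and no data are discarded. The tagging has to happen in the field: once bags from different streets are mixed, the matched analysis cannot be recovered.
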